**(15) Cases of death caused by SARS-CoV-2 variants and subvariants starting 14 days post-vaccination.**

**5.1.2.2 Immunogenicity endpoints**

**5.1.2.2.1 Prime immunization**

For participants in the immune subgroup, the following endpoints are defined for the assessment of neutralizing antibody against SARS-CoV-2 variants on Days 14 and 28 after vaccination.

**(1) Geometric mean titer (GMT) and geometric mean increase (GMI);**

**(2) Neutralizing antibody seroresponse rate**, where the seroresponse rate is defined as the proportion of participants whose antibody titer shifts from below LLOQ before study vaccination to  $\geq$  LLOQ after vaccination, or from  $\geq$  LLOQ before vaccination to  $\geq$  4-fold baseline after vaccination.

**5.1.2.2.2 Persistence study**

For participants in the immune subgroup participating in the immunogenicity persistence study, the following endpoints are similarly defined for immunogenicity assessment visits on Days 7, 14, 28, and 90 after vaccination and subsequent scheduled dates:

- (1) GMT and GMI of neutralizing antibody against SARS-CoV-2;**
- (2) Serum positive rate of neutralizing antibody against SARS-CoV-2.**

## 5.2 Safety endpoints

### (1) AEs

**Solicited AEs:** Injection site (local) AEs and non-injection site (systemic) AEs actively collected in the solicited period (within 0–7 days after vaccination).

- **Local AEs:** Injection site pain, injection site tenderness, injection site erythema, injection site swelling, injection site induration, and injection site pruritus.
- **Systemic AEs:** Fever, nausea, vomiting, headache, fatigue, myalgia, arthralgia, chills, and diarrhea.

**Unsolicited AEs:** All AEs except solicited AEs.

### (2) SAEs

### (3) AESIs

## 6. Analysis Sets

### (1) Full analysis set (FAS)

It includes all randomized participants who receive at least one dose of the investigational product (IP). Participants receiving a vaccine with an incorrect number are analyzed in the originally randomized treatment group according to the principle of intention to treat (ITT).

### (2) Per-protocol set (PPS)

It includes participants in the FAS except those with major protocol violations judged to have a significant impact on the evaluation of protective efficacy on 7 days after vaccination. Exclusion criteria are determined and documented jointly by the sponsor and the investigator prior to DBL and unblinding.

### (3) Per-protocol set for efficacy (PPE)

It includes the susceptible population in the PPS with negative PCR results at baseline (baseline IgG < 338 BAU/mL) with no evidence of infection within 7 days after vaccination. The PPE population is the primary analysis population for VE assessment 7 days post-vaccination.

### (4) Per-protocol set for efficacy-14 (PPE-14)

It includes the susceptible population in the PPS with negative PCR results at baseline (baseline

IgG < 338 BAU/mL) with no evidence of infection within 14 days after vaccination. The PPE-14 population is the primary analysis population for VE assessment 14 days post-vaccination .

**(5) Full analysis set for immunogenicity (I-FAS)**

It includes the population with vaccination of the investigational product, pre-vaccination immunogenicity baseline data, and at least one post-vaccination evaluable immunogenicity data in all immunogenicity subgroups.

**(6) Per-protocol set for immunogenicity (I-PPS)**

It includes participants in the I-FAS with no major protocol violation that affects the immunogenicity assessment on Day 28 after vaccination. Particularly, for participants with evidence of SARS-CoV-2 infection, post-infection immunogenicity data will be excluded from analysis, and pre-infection immunogenicity data may still be included.

**(7) Immunogenicity per-protocol evaluable (I-PPE)**

It includes the susceptible population in the PPS with negative PCR results at baseline (baseline IgG < 338 BAU/mL). The I-PPE is the primary analysis population for immunogenicity. Particularly, for participants with evidence of SARS-CoV-2 infection, post-infection immunogenicity data will be excluded from analysis, and pre-infection immunogenicity data may still be included.

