## 7.3 Demographic data and baseline characteristics

Demographic data and baseline characteristics will be analyzed based on FAS, PPE, PPE-14, and I-PPE.

The descriptive statistics of the following demographic data and baseline characteristics will be given separately for participants in each group:

- Demographic data (including age, sex, height, weight, BMI, ethnicity, and race);
- Clinical characteristics during the screening period (including whether the participant has history of COVID-19 infection, the time from the last infection to this vaccination (months), whether the COVID-19 vaccine has been vaccinated before enrollment, the time from the last previous dose to this vaccination (months), the vaccine type of the last previous dose, the number of doses vaccinated, the types of each dose of vaccine, rapid antigen test results, nucleic acid test results, HIV test results, stratification of anti-SARS-CoV-2 IgG antibody level, and anti-SARS-CoV-2 IgG antibody results);
- Follow-up time of cases (including follow-up time of cases on Day 7 after vaccination, follow-up time of cases on Day 14 after vaccination, and follow-up time of cases after vaccination);
- Baseline vital signs (including systolic blood pressure, diastolic blood pressure, respiratory rate, pulse, body temperature);
- Baseline physical examination (including general examination, head and neck, lymph nodes, skin, chest, abdomen, musculoskeletal system, and others).

Time from the last previous infection to this vaccination (months) = (Vaccination date - Last infection date + 1) / 30.4375; the time from the last previous dose to this vaccination (months) =

(Vaccination date - Last dose date + 1) / 30.4375.

The previous medications and vaccinations are coded according to WHO DD (Chinese version, 202209), and statistical description is performed on the number of previous medications/vaccinations, number of participants involved, and frequency of medications/vaccinations by ATC2 classification and drug name, respectively.

The past medical history is coded according to MedDRA (V25.1\_Chinese version), and statistical description is performed on the number of past medical history, number of participants involved, and frequency of past medical history by SOC and PT, respectively.

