**7.6.2.2 Immunogenicity**

**7.6.2.2.1 Prime immunization**

The main results of the immunogenicity analysis for the prime immunization will be based on the I-PPE population. The I-PPS will also be analyzed. Particularly, post-infection immunogenicity data for SARS-CoV-2 infection will be excluded from analysis, and pre-infection data may still be included. Exploratory analysis will also be performed on participants who are infected at baseline (positive for nucleic acid or antigen tests).

The GMT of neutralizing antibody against SARS-CoV-2 (including variants or mutant subtypes) in the immunogenicity subgroup at each time point post vaccination is analyzed by the covariance model. The model is constructed with antibody GMT post vaccination after logarithmic transformation at each time point as the dependent variable, antibody GMT before vaccination after logarithmic transformation at each time point as the covariate, the age (18–59 years,  $\geq 60$  years), the vaccine type of the last previous dose (inactivated, non-inactivated), and the group as fixed effects. The arithmetic mean of antibody post vaccination after logarithmic transformation at each time point in each group and the least squares mean (LSM) of the difference between groups are calculated according to the model; after inverse logarithmic transformation, the LSM and 95% confidence interval of antibody GMT and GMT ratio (test group / control group) at each time point post vaccination in each group are calculated.

The geometric mean and two-sided 95% confidence interval are used to statistically describe anti-SARS-CoV-2 neutralizing antibody GMT and GMI at each time point in the test group and the control group under the immunogenicity subgroup, respectively.

The seroresponse rates of anti-SARS-CoV-2 neutralizing antibody in the test group and control group at each time point post vaccination are calculated, respectively, and their 95% confidence

intervals are calculated by Clopper-Pearson method. The ratio difference (test group - control group) and its two-sided 95% confidence interval are calculated using the CMH- $\chi^2$  test including randomization stratification factors, and the difference between groups is statistically tested.

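### The SAP's primary immunogenicity set (I-PPE) omits the Day 28 violation filter and the titre-data requirements that its own I-PPS and I-FAS impose

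*Combined protocol and SAP*

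**What the plan says.** SAP section 6 has two branches of per-protocol sets.

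- **Efficacy branch.** Section 6(2) forms the PPS from the FAS, "except those with major protocol violations judged to have a significant impact on the evaluation of protective efficacy on 7 days after vaccination".
- **Immunogenicity branch.** Section 6(5) limits I-FAS to vaccinated members of the immunogenicity subgroup who have baseline titre data and "at least one post-vaccination evaluable immunogenicity data in all immunogenicity subgroups". Section 6(6) then defines I-PPS: "It includes participants in the I-FAS with no major protocol violation that affects the immunogenicity assessment on Day 28 after vaccination".

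Section 6(7) defines I-PPE from the first branch: "It includes the susceptible population in the PPS with negative PCR results at baseline (baseline IgG < 338 BAU/mL". It adds that titres obtained after an infection are left out, and it assigns the role: "The I-PPE is the primary analysis population for immunogenicity".

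I-PPE is then used throughout. Section 7.6.2.2.1 states: "The main results of the immunogenicity analysis for the prime immunization will be based on the I-PPE population", with I-PPS as a further analysis. Section 7.6.2.2.2 bases the persistence analysis on the I-PPE members who take part in the persistence study. Section 7.2 reports the size of each analysis set. Section 7.3 states: "Demographic data and baseline characteristics will be analyzed based on FAS, PPE, PPE-14, and I-PPE".

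The Protocol Synopsis (Statistical populations) differs. It names I-PPS as the main immunogenicity set and builds it from the PPS plus valid titres before and after vaccination. Its PPS removes deviations that could affect critical or key study data, which is wider than the SAP's rule. SAP section 2.3 nevertheless declares no change from the protocol.

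**The concern.** A per-protocol immunogenicity set should remove people whose titres are unreliable because of a protocol violation, and should contain only people with titres to analyse. I-PPE takes its violation rule from a set designed for efficacy, and section 6(7) refers to neither I-FAS nor I-PPS. Its wording is that of PPE in section 6(3) without the early-infection condition.

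The results affected are the primary GMT, GMT ratio and seroresponse comparisons and the persistence analysis, which cover secondary endpoints of the trial. In addition, I-PPE is not a subset of I-PPS. A difference between the primary and supporting results would mix the effect of restricting to susceptible participants with the effect of different violation rules. Two programmers could also build different I-PPE sets, one literal and one as apparently intended.

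**Working it through.** The plan gives no count for I-PPE or I-PPS, so there is no stated figure to reproduce. The check compares the definitions and then bounds the head count.

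**1. Definitions side by side (SAP section 6)**

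| Set | Parent | Violations removed | Titre data required | Further conditions |
|---|---|---|---|---|
| PPS | FAS | those affecting 7-day efficacy | none | none |
| PPE | PPS | as PPS | none | PCR negative, IgG < 338, no infection within 7 days |
| I-FAS | vaccinated members of immunogenicity subgroup | none | baseline and at least one post-dose | none |
| I-PPS | I-FAS | those affecting Day 28 immunogenicity | through I-FAS | post-infection titres dropped |
| I-PPE | PPS | as PPS | none | PCR negative, IgG < 338; post-infection titres dropped |

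**2. Test records, all PCR negative with IgG 100 BAU/mL**

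- *Record A:* a subgroup member whose single major violation invalidates the Day 28 titre but has no bearing on 7-day efficacy. In PPS, so in I-PPE. Not in I-PPS. The titre enters the primary result only.
- *Record B:* a participant outside the subgroup with no violation. In PPS, so in I-PPE, but with no neutralising-antibody sample.
- *Record C:* a subgroup member with sound titres and a violation that matters only for efficacy. Not in PPS, so not in I-PPE, but in I-PPS.

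Records A and C together show that neither set contains the other among susceptible subgroup members.

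**3. Size of the literal set**

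PPE has every condition of I-PPE plus freedom from early infection, so PPE is contained in I-PPE.

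- PPE = 2,623 (Supplementary Appendix, Table S2), so literal I-PPE ≥ 2,623. Table S2 shows three of these with a missing baseline nucleic acid result; a strict reading gives 2,620, which changes nothing below.
- FAS = 9,196 (Table S1). Subgroup share 5–10% (SAP 4.1): 0.05 × 9,196 = 460 to 0.10 × 9,196 = 920.
- PPE share of FAS = 2,623 / 9,196 = 0.285.
- Expected sampled PPE members, if the subgroup is representative: 0.285 × 460 ≈ 131 to 0.285 × 920 ≈ 262.
- Expected PPE members without a neutralising-antibody sample: 2,623 − 262 = 2,361 to 2,623 − 131 = 2,492.
- Extreme floor, if a full 10% subgroup fell entirely inside PPE: 2,623 − 920 ≈ 1,703.

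**4. Effect on titres**

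Record B has no titre and cannot enter a GMT or a rate. For record A, if a fraction *p* of an arm has titres wrong by a factor *k*, that arm's unadjusted GMT is multiplied by *k*^*p*. For a common *k*, the ratio is multiplied by *k* raised to the difference in *p* between arms, which is 1 when *p* is the same in both. The documents give neither *p* nor *k*, so no shift can be computed.

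**The case against.** The other side has good points.

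- **PPS is not a mistaken parent.** A reader might infer that I-PPE was simply hung on the wrong set. The protocol's own I-PPS is built on the PPS, and under the protocol's wider PPS rule record A could be excluded. The gap comes from the SAP's narrower PPS combined with the missing I-FAS and I-PPS conditions.
- **Some exclusion does apply.** A reader might infer that nothing specific to immunogenicity is removed. Sections 6(7) and 7.6.2.2.1 both drop post-infection titres. What is missing is the violation filter.
- **Unsampled members do not distort titres.** The large literal count invites that inference, but section 7.6.2.2.1 confines the GMT model to the subgroup, 7.1.1 uses valid results as the percentage denominator, 7.6.2.2.2 limits persistence to persistence-study members, and 7.8 does not fill in missing immunogenicity data. They also do have a baseline anti-spike IgG result (Table S2); only neutralising-antibody samples are lacking.
- **Partial safeguards for record A.** The I-PPS analysis would show a material effect, and section 6 settles set membership at a data review meeting. Section 7.1.3 disregards visits outside the protocol, and the Schedule of Activities gives Day 28 a window of +7 days, so a badly mistimed sample might be caught.
- **Low inferential weight.** Section 7.10 makes immunogenicity P values nominal.

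These points limit the consequences. They do not remove the gap: the meeting is given no rule that adds the Day 28 filter to I-PPE, 7.1.3 is unclear on late samples and silent on other violations, and a supporting analysis does not correct the primary one.

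**Conclusion.** The definition is wrong as written, and the severity is minor. I-PPE lacks the Day 28 violation filter and the subgroup and titre-data conditions. The first omission can let unreliable titres into the primary immunogenicity results. The number of people concerned is unknown, and it is zero if no subgroup member has a violation that matters for Day 28 titres alone. A reader might infer a material shift in the GMT ratio. The documents give no violation frequency or titre error to support one, and equal proportional shifts in both arms would cancel.

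The second omission affects only the I-PPE count (7.2) and baseline table (7.3): at least 2,623 people as written, against about 131 to 262 of them expected to be sampled. That range assumes a representative 5–10% subgroup of the 9,196 in the FAS. The primary efficacy result is untouched.

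**What to change.** Redefine I-PPE in SAP section 6(7) as participants who belong to both the PPS and the I-PPS, with a negative baseline PCR and baseline IgG < 338 BAU/mL. Keep the post-infection exclusion, and use this set in 7.2, 7.3, 7.6.2.2.1 and 7.6.2.2.2 (in the last, for those in the persistence study).

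Replacing PPS by I-PPS alone would not do. The SAP's I-PPS does not require PPS membership, so people with efficacy-related major violations, whom the current text and the protocol's PPS-based I-PPS keep out, could enter.

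Also reconcile the main immunogenicity set, which is I-PPS in the protocol and I-PPE in the SAP, and correct the no-change statement in SAP 2.3. If the titre analysis has already been run, state which definition was programmed.

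The cost is a few words and no new data. A few participants with immunogenicity-relevant violations leave the primary set. People with sound titres but an efficacy-only violation stay out, as they do now. I-PPE becomes a subset of I-PPS, although the two will still differ in PPS membership as well as susceptibility.

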**(8) Safety set (SS)**

It includes all participants who receive one dose of the investigational product (IP). The participants receiving a vaccine with an incorrect number are analyzed in the group of the treatment that they actually receive. Participants who are not randomized but receive the study vaccine will not be included in the safety set, and their safety data will be presented separately.

The safety set is mainly used for safety evaluation of the vaccine.

The protective efficacy of the vaccine will also be assessed among the population in the per-protocol set with positive evidence before the exclusion analysis target date (such as 7/14 days) and other populations.

The above analysis sets will be determined by the sponsor, the principal investigator, statisticians and data manager together at the data review meeting.

## **7. Statistical Analysis Methods**

### **7.1 General considerations**

#### **7.1.1 General analytical methods**

➤ **Descriptive statistics**

Unless otherwise stated, the following descriptive statistical summaries are given by variable type:

- ✓ Continuous variables are summarized with the mean, standard deviation, median, minimum, and maximum.
- ✓ Categorical or ordinal variables are summarized with the frequency and percentage, where the denominator for percentage calculation is the number of participants with valid results in the corresponding analysis set.

➤ **Decimal places**

Unless otherwise specified, the decimal places in the analysis report are implemented according to the following rules:

- ✓ Consistent with the largest number of decimal places of the original data for the minimum and maximum;
- ✓ One more digit than the largest number of decimal places of the original data for the median, mean, and standard deviation;
- ✓ Two decimal places for the percentage, rate, and rate difference;
- ✓ Four decimal places if the P value is  $\geq 0.0001$ ; reported as “ $< 0.0001$ ” if the P value is  $< 0.0001$ ;
- ✓ Three decimal places for test statistics in all statistical tests;
- ✓ Two decimal places for derived data.

### 7.1.2 Related definitions and derivative rules

➤ **Baseline**

Unless otherwise stated, baseline is defined as the last non-missing value measured prior to vaccination.

➤ **Conversion of years, months and days**

Month = days / 30.4375, Year = days / 365.25, rounded to one decimal place.

➤ **Duration of study**

Taking the vaccination date as the study start date, the duration of study corresponding to the examination or event is calculated based on the study start date according to the following formula:

Duration of study = Examination date - Study start date.

➤ **Adverse Events**

AE onset time (days) = Onset date of AE - Vaccination date.

Duration of AE (days) = End date of AE - Onset date of AE + 1.

➤ **Treatment emergent adverse events (TEAEs)**

TEAEs are defined as the adverse events that occur after vaccination (including the day of vaccination), and occur before vaccination but worsen after vaccination, and are programmed

according to the following rules:

- ✧ An AE that occurs after/on the vaccination date is counted as TEAE;
- ✧ An AE that occur before the vaccination date is counted as non-TEAE;
- ✧ If the onset time of an AE or the vaccination date is missing so that it is impossible to clearly determine whether the AE occurs after the first-dose vaccination, the AE is counted as TEAE.

The study is designed to statistically analyze the **TEAEs**, including AEs occurring within 28 days after vaccination. AEs that occur before vaccination and 28 days after vaccination are listed separately. Unless otherwise specified, the AEs described below are TEAEs.

➤ **Coding**

Adverse events and past medical history are coded according to the Chinese version of the *Medical Dictionary for Regulatory Activities* (MedDRA) V25.1. Previous and concomitant medications and previous and concomitant vaccinations are coded according to the Chinese version of the *World Health Organization Drug Dictionary* (WHO DD), 202209.

➤ **Previous and concomitant medications**

The following rules are adopted for the judgment of previous and concomitant medications:

- ✧ Medications with an end date prior to the vaccination date are counted as previous medications.
- ✧ Medications that start before/on and end after the vaccination date, or start after the vaccination date, are counted as concomitant medications.

➤ **Previous and concomitant vaccinations**

The judgment rules for previous and concomitant vaccinations are the same as those for previous/concomitant medications.

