|                                            | 
SAEs and AESIs will be actively monitored for about 365 days after the study vaccination.
 
IDMC: An Independent Data Monitoring Committee (IDMC) will be set up to review the safety data after the study vaccination,
 
Participants can choose whether to be blinded or not after obtaining statistically significant vaccine efficacy and adequate safety data. Participants will be encouraged to remain in the ongoing study until the end of the study, unless they request to withdraw from the study for any reason. SAEs and AESIs would be monitored during this time.
 
For participants who request to be unblinded and are confirmed to be placebo recipients, the following procedure is available:
 
 
1) remain in the study for continued follow-up;
 
2) withdraw from the study by vaccination with other marketed vaccines;
 
3) withdraw from the study for other reasons.
 
 
Participants who receive or request any other COVID-19 vaccination during the study should withdraw from the study.
 |
| 
Total Number of Participants
 | 
Approximately 10,000 participants are planned to be enrolled. The percentage of participants aged <math>\geq 60</math> years shouldn't be less than 20%, and the percentage of participants who have received 3 doses of inactive COVID-19 vaccines shouldn't be less than 60%. The exact number of participants enrolled in the study will depend on the infection rate of COVID-19 at the time of the enrollment and the true VE (vaccine efficacy) of SCTV01E. If the attack rate is much higher, case accrual would be expected to be more rapid, enabling the study's primary endpoint to be evaluated much sooner and the actual enrolled sample size may be less than planned.
                                                                                                                                                                                                                                                                                                                                                                                                                         |

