#### **7.7.2 SAEs**

The number of participants and incidence of SAEs in each group are calculated as follows:

- All SAEs;
- SAEs related to the study vaccine;
- SAEs related to the study vaccine with severity  $\geq$  Grade 3;

A list of SAEs is provided.

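### SAP 7.1.2 defines worsened pre-vaccination events as TEAEs, but its programming rule classes every event with onset before vaccination as non-TEAE

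*Combined protocol and SAP*

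**What the plan says.** SAP 7.1.2 defines TEAEs in two limbs: events that arise on or after the day of vaccination, and events that "occur before vaccination but worsen after vaccination". It then gives three programming rules:

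- "An AE that occurs after/on the vaccination date is counted as TEAE".
- "An AE that occur before the vaccination date is counted as non-TEAE".
- An event is counted as a TEAE if a missing date makes it impossible to tell whether it came before or after vaccination.

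The next paragraph describes the TEAE analysis as "including AEs occurring within 28 days after vaccination" and adds that "AEs that occur before vaccination and 28 days after vaccination are listed separately". It closes with a default: "Unless otherwise specified, the AEs described below are TEAEs".

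The protocol synopsis (Safety Analysis) says that TEAEs are summarised and that adverse medical conditions present before vaccination are listed. It does not mention worsening.

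SAP 7.7.2 opens with "The number of participants and incidence of SAEs in each group are calculated as follows", and its first line is all SAEs. SAP 7.7.3 does the same for AESIs. Neither gives a day limit. The protocol synopsis says that "SAEs and AESIs will be actively monitored for about 365 days after the study vaccination".

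**The concern.** The programming rules decide which records reach the tables. The second rule sorts by onset date alone, so the second limb of the definition can never be met by an event that keeps its pre-vaccination onset date. The rules are also uneven: an event of unknown timing is conservatively counted, while a documented worsening after vaccination is not.

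What is at stake is the completeness of the AE incidence tables in SAP 7.7.1. The rule treats both arms alike, but it does not follow that the between-arm comparison is unaffected. If the vaccine made pre-existing events worse more often than placebo did, the excluded events would fall mainly in the vaccine arm, and the tables would understate that difference.

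The population includes people to whom this could apply. Inclusion criterion 6 admits participants with stable pre-existing conditions. Table S1 shows 1,984 of 9,196 (21.6%) with comorbidities and 1,349 of 9,196 (14.7%) with a positive baseline nucleic acid test. These figures show who could be exposed to the rule. They do not count lost events.

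**Working it through.** **1. Definition against rules.** No formula applies here, so the two texts in SAP 7.1.2 are set side by side.

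| Event | By the definition | By the programming rules |
|---|---|---|
| Onset on or after the vaccination date | TEAE | TEAE |
| Onset before, no worsening | Not a TEAE | Non-TEAE |
| Onset before, worsens after | **TEAE** | **Non-TEAE** |
| Order unknown because a date is missing | Not addressed | TEAE |

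The texts conflict in the third row only. Nothing else in the SAP or the protocol synopsis resolves it: the synopsis only lists pre-vaccination conditions, and SAP 7.7.1 does not mention worsening.

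**2. Size.** A count would need the number of events with onset before vaccination and a later increase in severity. The documents give no such number, and no assumption in them leads to one. They do give reasons to expect it to be small:

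- Screening runs from Day -7 to Day 0 (Schedule of Activities).
- Solicited and unsolicited AEs are collected from Day 0 (Schedule of Activities, note 11).
- Pre-existing conditions must have been stable for at least 3 months (inclusion criterion 6).
- Recent fever and acute illness are exclusions (criteria 3 and 13).

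**3. Does the 28-day default also cut the SAE and AESI tables?** The wording leaves room for the question. The first programming rule has no upper day limit, the following paragraph sets 28 days, and 7.7.2 and 7.7.3 come after the default without naming a window. Table S6 shows how the tables were reported. Check: SAEs within 28 days plus SAEs after 28 days, against the row for any SAE; then any SAE / N.

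| Table S6 column | Within 28 days | After 28 days | Sum | Any SAE, stated | N | Any SAE / N |
|---|---|---|---|---|---|---|
| Baseline-negative, placebo | 13 | 19 | 32 | 32 | 3879 | 0.82% (stated 0.8) |
| Baseline-negative, SCTV01E | 19 | 17 | 36 | 36 | 3967 | 0.91% (stated 0.9) |
| Baseline-positive, placebo | 4 | 2 | 6 | 6 | 716 | 0.84% (stated 0.8) |
| Baseline-positive, SCTV01E | 1 | 3 | 4 | 4 | 634 | 0.63% (stated 0.6) |

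By arm, placebo has 17 + 21 = 38 of 4595, and SCTV01E has 20 + 20 = 40 of 4601. Every SAE total includes participants with events after Day 28. The TEAE total, by contrast, equals its 28-day row in all four columns (423, 851, 54, 88). The reported analysis therefore applied the 28-day limit to general TEAEs and not to SAEs. AESIs were 0 in every column, so they cannot test the point.

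**The case against.** **On the worsening rule.** The best defence is that the rules sort by recorded onset date, and many data-capture conventions record a worsening as a new event with a new onset date. Under such a convention the first rule would catch it and nothing would be lost. This stands as a possibility. The public documents contain the protocol synopsis but no AE-recording section, so the convention cannot be confirmed. Even if it applies, the SAP should say so, because the rule as written does not depend on it. The further defence that few events are exposed is reasonable and is accepted above.

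**On the 28-day window.** A reader might infer that SAEs and AESIs after Day 28 are listed but left out of the incidence tables, and that the 41 of 78 participants with later SAEs in Table S6 (21 + 20 of 38 + 40) measure the loss. The documents do not support this:

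- SAP 5.2 and 7.7 treat AEs, SAEs and AESIs as three separate categories, and 7.7.2 and 7.7.3 ask for the incidence of all SAEs and all AESIs.
- The protocol's safety endpoints set day limits for solicited and unsolicited AEs and none for SAEs and AESIs.
- SAP 4.1 collects SAEs and AESIs until the participant completes or leaves the study.
- The 41 participants come from the incidence table itself and are counted in its totals.

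Limiting general TEAE tables to 28 days is not an error either. It matches the Day 0 to Day 28 collection of unsolicited AEs.

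**Conclusion.** The point holds for the worsening rule. SAP 7.1.2 counts a worsened pre-vaccination event as a TEAE in its definition and as a non-TEAE in its programming rule, and no other text in the documents settles which governs. Followed literally, the rule removes these events from the TEAE tables. This rests on one assumption, that worsening is not recorded as a new AE with a new onset date.

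The number of events affected cannot be derived and is probably small. It would be too strong to say that post-vaccination worsening is never counted, or that the reported safety tables are materially understated.

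For SAEs and AESIs only a wording ambiguity remains: a general default placed ahead of two sections that state no window. Table S6 shows reporting and not planning, but it agrees with the plan's own text that these tables cover the whole study.

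**What to change.** Replace the second programming rule in SAP 7.1.2 with: *An AE with onset before vaccination is non-TEAE unless its severity increases after vaccination, in which case it is a TEAE.* If worsening is in fact recorded as a new event, add a sentence saying so and keep the definition and rule consistent with it.

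Optionally, add to SAP 7.7.2 and 7.7.3: *SAE and AESI tables include all events from Day 0 to end of study.* This confirms what the plan already indicates and prevents the 28-day default from being misread onto them.

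The cost is one sentence, a second if the clarification is adopted, and a small change to the TEAE flag derivation. The flag change needs post-vaccination severity to be available for events that began before vaccination, which should be checked against the data collected.
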